### Statistical methods

2.9.

The demographics will be reported at exact values for each arm to characterize each arm.

Full completion of all datasets in a clinical trial like this is unlikely; therefore, two different populations will be used for analysis. The first population will be used to assess the effect of the treatment and will be the per protocol population (PPP). The PPP is defined by all data points available for analysis. The other population is the intention to treat (ITT) population. The ITT will be used when assessing safety and feasibility outcomes. This is to ensure that participants who drop-out due to adverse events are being evaluated as part of the study.

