### Withdrawal and drop-out

2.7.

All participants are free to withdraw from the study at any time and are not required to give any reason for doing so. If a participant at any time does not fulfill the in- and exclusion criteria, they will be withdrawn from the study, except if this is solely the progression from moderate to severe AD. The principal investigator may additionally halt the trial for an individual participant or the entire trial, should there be any major safety concerns with the continuation of the study.

In case of drop-outs or missing data for any other reason, a last observation carried forward approach will be used to handle the missing data.

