### Recruitment and sample size

2.8.

Participants will be recruited through contact with their usual healthcare professionals on the Danish Island of Zealand with a population of approximately 2.7 million inhabitants (Danmarks Statistik, 2021).

The sample size calculation is based on the primary outcome and has been based on effect sizes reported (Xing et al., 2018; Jones et al., 2019). The estimation is carried out using R version 3.6.3 with “pwr” version 1.2–2 with the following assumptions: (1) Two-sample *T*-test assuming equal variance, (2) Equal allocation, (3) Signal-to-noise (SNR) ratio at 40 Hz of 2.7 dB in the active treatment group and 0 dB in the placebo group at 6 months, (4) Standard deviation of 3.2 dB in both groups, (5) A power of 90%, and (6) Type 1 error of 5%. A 50% drop-out rate is assumed based on previous experience, resulting in a sample size of 124 (62 in each arm).

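### The only stated efficacy population is an available-case set labelled per protocol, with no all-randomised efficacy analysis despite an assumed 50% drop-out, and it does not fit the LOCF rule

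*Protocol article*

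**What the plan says.** All references are to the protocol article.

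- **Section 2.9, efficacy:** "The first population will be used to assess the effect of the treatment and will be the per protocol population (PPP"). Its whole definition is: "The PPP is defined by all data points available for analysis".
- **Section 2.9, ITT:** "The ITT will be used when assessing safety and feasibility outcomes". The reason given is: "This is to ensure that participants who drop-out due to adverse events are being evaluated as part of the study".
- **Section 2.7, missing data:** for drop-outs and any other missing data, "a last observation carried forward approach will be used to handle the missing data".
- **Section 2.7, withdrawal by the study:** "If a participant at any time does not fulfill the in- and exclusion criteria, they will be withdrawn from the study", unless the only reason is progression to severe disease.
- **Section 2.8:** "A 50% drop-out rate is assumed based on previous experience, resulting in a sample size of 124 (62 in each arm").
- **Section 2.5:** the battery is given at weeks 0, 26 and 32, and the SSVEP recording at weeks 0 and 26 only.
- **Section 2.6:** the primary question is whether active and placebo differ from baseline to week 26. The device camera records days missed, time present and gaze direction.

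**The concern.** The trial tests for a difference between active and placebo, so its main estimate should compare the groups as randomised. The plan instead takes efficacy from whoever has data. Having week-26 data is decided after randomisation: it depends on coping with six months of daily one-hour sessions, on caregiver support, and on whether the study withdraws the participant under section 2.7. If those factors relate to outcome differently in the two arms, the comparison is biased.

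The label adds a second problem. A per-protocol set normally excludes poor adherers and major deviations. This one names no such rule, so it does not estimate the effect in adherers and does not secure the randomised groups either. The reason section 2.9 gives for using ITT, keeping people who leave because of adverse events in the evaluation, applies equally to efficacy, but is not applied there.

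The third problem is that sections 2.7 and 2.9 cannot both be followed without further explanation. A set made of available data needs no imputation, and a LOCF rule implies that people without data are included.

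**Working it through.** **1. The plan's own sample size.** Inputs from section 2.8: difference 2.7 dB, SD 3.2 dB, two-sample t-test, power 90%, type I error 5% (taken as two-sided, which reproduces the figure), equal allocation, 50% drop-out.

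- Standardised effect: 2.7 / 3.2 = 0.844.
- Noncentral t calculation: n = 30.51, so 31 per arm (power 90.5%).
- Inflation: 31 / (1 − 0.5) = 62 per arm, 124 in total.

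The stated 124 reproduces. The power therefore rests on 31 participants per arm with data out of 62 randomised.

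**2. The two readings of the efficacy set.**

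| Reading | Who is compared at week 26 | Value for someone lost before week 26 |
|---|---|---|
| Section 2.9 alone (available data) | those with week-26 data, about 50% if the assumed drop-out occurs | none |
| Section 2.9 with LOCF from section 2.7 | could approach all randomised participants with a baseline | baseline, hence zero change |

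The second row follows from section 2.5: there is no visit with this battery between weeks 0 and 26, so the only earlier observation is baseline.

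**3. How selective drop-out becomes bias.** Let p be the drop-out proportion in an arm and δ the completer mean minus the drop-out mean. The completer mean exceeds the full-arm mean by p × δ, so the bias of the available-case difference is p1 × δ1 − p0 × δ0 (1 = active, 0 = placebo). With equal p and equal δ it is zero. With p = 0.5 in both arms, a bias of 0.1, 0.2 or 0.3 SD needs δ1 − δ0 = 0.2, 0.4 or 0.6 SD.

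**4. Effect on the type I error.** Assume no true effect and completers' arms that differ by b SD. The test statistic is noncentral t with 2n − 2 degrees of freedom and noncentrality b × √(n/2). For n = 31, √(31/2) = 3.94.

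| Assumed b | In dB (b × 3.2) | Type I error, 31 completers per arm | Type I error, 16 completers per arm |
|---|---|---|---|
| 0.1 | 0.32 | 6.7% | 5.9% |
| 0.2 | 0.64 | 12.1% | 8.5% |
| 0.3 | 0.96 | 21.3% | 13.0% |

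The last column is about half of 31, relevant if the recruitment target in section 2.2 (31 included per arm) is the one that applies.

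**5. Why the direction is open.** Take one assumed case: 50% drop-out in both arms, active completers 1.6 dB (0.5 SD) above active drop-outs, placebo drop-out unrelated to outcome, and placebo mean change zero.

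- *True effect 2.7 dB.* The active completer mean is 2.7 + 0.5 × 1.6 = 3.5 dB. Available data give 3.5, a bias of +0.8 dB. LOCF gives 0.5 × 3.5 + 0.5 × 0 = 1.75, a bias of 1.75 − 2.7 = −0.95 dB.
- *No true effect.* The active completer mean is 0.5 × 1.6 = 0.8 dB. Available data give a bias of +0.8 dB. LOCF gives 0.5 × 0.8 = +0.4 dB.

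The same drop-out pattern can therefore inflate or shrink the estimate, depending on which of the two sections governs.

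**The case against.** **LOCF puts the drop-outs back.** Section 2.7 covers drop-outs explicitly, so the efficacy set may come close to everyone randomised. This stands in part. A reader might infer from section 2.9 that half the randomised participants are certainly outside the efficacy comparison, and the documents do not establish that. But section 2.9 does not say that imputed values count as available, and carrying baseline forward assigns no change in a progressive disease. Neither reading gives a sound all-randomised estimate.

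**The fault is mostly one of labelling.** With no exclusion of non-adherers, the set is closer to an observed-case full analysis set than to a true per-protocol set. This is fair, and is why the risk lies in selective drop-out and missing data, not in removing poor adherers. Renaming alone would still leave no stated all-randomised efficacy analysis.

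**Blinding limits differential drop-out.** Section 2.4 describes devices that look alike, with participants, caregivers and investigators blinded. That makes arm-specific loss less likely but does not rule it out. The drop-out gaps used above are all assumed.

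**The analysis plan may settle it.** Section 2.6 promises one. But section 2.9 does not leave the choice open: it assigns efficacy to one population and ITT to other outcomes.

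**Conclusion.** The point holds in this form. The article fixes an available-case set, misnamed per protocol, as its only efficacy population. It states no all-randomised efficacy analysis while assuming 50% drop-out, and it leaves that set unreconciled with its LOCF rule. That selective drop-out can bias the primary comparison follows from the text. Its size and direction do not. The 7% to 21% type I error range rests on an assumed imbalance of 0.1 to 0.3 SD, no true effect and 31 completers per arm.

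Two stronger readings should be resisted. One is that a positive result could not be attributed to the device: even the assumed +0.8 dB is 0.8 / 2.7 = 30% of the planned effect, and under LOCF the bias can run the other way. The other is that ITT is kept for safety alone: section 2.9 also uses it for feasibility.

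**What to change.** Before unblinding:

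1. In section 2.9, make the primary efficacy population all randomised participants, by allocated arm.
2. Analyse it with a baseline-adjusted likelihood-based model that uses all observed values, in place of LOCF, and add a sensitivity analysis for data not missing at random.
3. Reconcile section 2.7 with section 2.9, so that one rule covers drop-outs and missing data.
4. Rename the present per-protocol population as the available-case set.
5. Define a true per-protocol set from the adherence data the device already records, fix it before unblinding, and use it only as a sensitivity analysis.

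The cost is revised wording in two sections, a little more analysis, and possibly a smaller effect estimate. The model has a limit that should be stated: participants lost before week 26 contribute little beyond baseline, so it removes only the bias that observed data explain. That is why the sensitivity analysis in step 2 is needed.

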### Measurements

2.5.

At the inclusion visit (week −3 to 0), after giving informed consent, the following baseline characteristics will be recorded during a pre-screening: Age (years), gender (male/female), ethnicity (White, black, or others), height (cm), weight (kg), alcohol use in units (one unit defined as 12 g pure alcohol), tobacco use (package years), time since diagnosis of AD (months) and education (years). The participants will further have their medical history reviewed including current medication, physical examination, and blood samples (plasma-Alat, plasma-HbA1C, plasma-Sodium, plasma-Potassium, and plasma-Creatinine), this is done to rule out any undiagnosed diseases and establish baseline values in case of adverse events. To assess the effects of the treatment, the following examination battery will be administered at baseline (week 0), post-intervention follow-up (week 26), and no-intervention follow-up (week 32): EEG steady state visual evoked potential (SSVEP) during exposure to the allocated device (not at week 32), resting-state electroencephalography (rs-EEG) (Cassani et al., 2018), Alzheimer’s Disease Assessment Scale-Cognitive Subscale Plus Executive Function & Functional Ability (ADAS-Cog Plus EF&FA) (Skinner et al., 2012), Alzheimer’s Disease Cooperative Study – Activities of Daily Living (ADCS-ADL) (Galasko et al., 1997), Montreal Cognitive Assessment (MoCA) (Nasreddine et al., 2005), Magnetic resonance (MR) imaging (high-resolution T1-weighted imaging, functional Blood Oxygen Level Dependent imaging (BOLD-fMRI), perfusion-weighted MR imaging and MR spectroscopy) and blood-based biomarkers (plasma Aβ42/40-ratio, plasma tau181, plasma tau231, plasma neurofilament light chain, and plasma glial fibrillary acidic protein). In addition to these time-specific measurements, continuous actigraphy will be collected by a wrist-worn actigraph to assess activity and changes in the circadian rhythm. All data will be recorded by trained personnel. The EEG will be recorded in a designated room, shielded from outside electrical interference using 25 gel-mounted electrodes arranged according to the international 10–20 system with additional electrooculographic (EOG) and electrocardiographic (ECG) electrodes. The cognitive testing will be performed by trained personnel with experience in neuropsychological testing. The MR scan will be performed on a 3T scanner (Siemens Magnetom Vida, Siemens Healthcare). Actigraphy will be recorded using a wrist-worn actigraph (ScanWatch, Withings).

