
### Outcome measures

2.6.

Primary outcome:

The goal is to determine the total gamma power, with no concomitant LTS device stimulation, and to assess changes in the gamma power at around 40 Hz measured with power spectral density and EEG SSVEP from baseline (week 0) to post-intervention follow-up (week 26).

Null hypothesis: There is no significant difference between treatment and placebo in total gamma power and power spectral density signal-to-noise ratio at baseline (week 0) and follow-up (week 26).Research hypothesis: There is a significant difference between treatment and placebo in total gamma power and power spectral density signal-to-noise ratio at baseline (week 0) and follow-up (week 26).

The statistical analysis plan will be available before the data collection of the study is completed.

Secondary outcomes:

The secondary outcomes include exploratory outcomes which are listed below. All refer to the change from baseline (week 0) to post-intervention follow-up (week 26), and no-intervention follow-up (week 32), unless otherwise specified.

Change in ADAS-Cog Plus EF&FAChange in ADCS-ADLChange in MoCAChange in resting-state BOLD-fMRI connectivity in the default mode network (DMN)Change in rs-EEG connectivity encompass alpha-theta with DMNChange in MR spectroscopy NAA/mI-ratioChange in total sleep time and wakefulness after sleep onsetChange in blood-based biomarkers of AD (plasma Aβ42/40-ratio, plasma tau181, plasma tau231, plasma neurofilament light chain, and plasma glial fibrillary acidic protein)Change in global atrophy (ventricular volume) and in hippocampal volumeChange in MR Arterial Spin labeling (ASL) perfusion in the posterior cingulate gyrus, precuneus, inferior parietal lobe, and lateral prefrontal cortexChange in rs-EEG spectral composition in the dominant alpha rhythm

In addition to these secondary endpoints, safety will be monitored by the number of Adverse Events (AE), and similarly, occurrences of ARIAs will be monitored. The compliance/adherence will be measured directly by the device which includes a camera with facial recognition software. This determines the number of days missed, the time present in front of the device as well as gaze direction to assess the time of direct exposure. Furthermore, compliance and feasibility will be evaluated via a structured interview that includes questions on the perception of flickering, brightness, and usability of the device.

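### Read as written, ITT plus LOCF counts participants with no MR after baseline as free of new ARIA, so absolute ARIA incidence is biased downward

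*Protocol article*

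**What the plan says.** Five provisions of the protocol article meet on this point.

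- **Outcome (2.6).** ARIA is a safety item next to adverse events: "safety will be monitored by the number of Adverse Events (AE), and similarly, occurrences of ARIAs will be monitored". No denominator or estimator is given for it.
- **Scan schedule (2.5).** MR imaging belongs to a set of assessments with fixed dates: "the following examination battery will be administered at baseline (week 0), post-intervention follow-up (week 26), and no-intervention follow-up (week 32"). The intervention ends at week 26 (2.1), so no MR is scheduled between the first and the last exposure.
- **Population (2.9).** "The ITT will be used when assessing safety and feasibility outcomes". The reason given is: "This is to ensure that participants who drop-out due to adverse events are being evaluated as part of the study".
- **Missing data (2.7).** Missing values, whether from drop-out or another cause, are filled by LOCF. The rule is general and does not exclude safety outcomes. No withdrawal scan is described.
- **Drop-out (2.8).** "A 50% drop-out rate is assumed based on previous experience". Its timing is not stated.

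**The concern.** An adverse event can be reported by a participant who has stopped, so the ITT population suits a count of adverse events. ARIA is a scan finding. A participant with no scan after starting the device has not been evaluated for it, whatever population they belong to, so the reason that 2.9 gives for using ITT fails for this one outcome.

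The two general rules then act together. ITT keeps the unscanned participant in the denominator. LOCF supplies a value, and for someone who leaves before week 26 the last MR is the baseline scan taken before exposure. Carried forward, it records no new ARIA.

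The result matters to the article's own argument. The Introduction presents ARIA as a known risk of amyloid-modifying agents and a reason to seek safer options, and the Discussion expects this intervention to reduce amyloid. A low ARIA figure would be read as an important safety result, and part of it could come from participants who were never scanned after exposure.

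**Working it through.** **1. The plan's own figure.** Inputs from 2.8: 2.7 dB against 0 dB, SD 3.2 dB, power 90%, type 1 error 5% (taken as two-sided, which the article does not state), equal allocation. Standardised effect = 2.7/3.2 = 0.844. The two-sample t-test needs 30.51, rounded up to 31 per arm. With 50% drop-out, 31/(1 − 0.5) = 62 per arm, 124 in total. This reproduces 2.8, where 31 is the number left after drop-out. Section 2.2 instead sets 31 per arm as the recruitment target. The sections conflict, so both readings are carried below.

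**2. One participant traced through the rules.** Baseline MR at week 0; leaves at, say, week 12; no later MR. Under 2.9 the participant is in the ITT denominator. Under 2.7 the missing week 26 and week 32 results take the week 0 value. Contribution to the ARIA rate: 0 in the numerator, 1 in the denominator.

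**3. Size of the bias at equal risk.** Let d be the drop-out proportion and s the share of drop-outs who have a post-baseline scan. If drop-outs and completers have the same ARIA risk, reported/true = 1 − d(1 − s).

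| d | s | reported/true |
|---|---|---|
| 0.5 | 0 | 0.50 |
| 0.5 | 0.5 | 0.75 |
| 0.5 | 1 | 1.00 |
| 0.2 | 0 | 0.80 |

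Illustration with 62 per arm, d = 0.5 and s = 0. The article gives no ARIA rate, so the true risk is assumed. At 10%, 31 × 0.10 = 3.1 cases are expected among the 31 scanned; 3.1/62 = 5%, against 3.1/31 = 10%. At 5% the reported figure is 2.5%, and at 20% it is 10%.

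**4. Unequal risk.** Let RR be the ARIA risk of drop-outs relative to completers, with d = 0.5 and s = 0. With the ITT denominator, reported/true = (1 − d)/[(1 − d) + d·RR]. With only scanned participants in the denominator it is 1/[(1 − d) + d·RR].

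| RR | ITT with LOCF | scanned only |
|---|---|---|
| 0.5 | 0.67 | 1.33 |
| 1 | 0.50 | 1.00 |
| 2 | 0.33 | 0.67 |
| 3 | 0.25 | 0.50 |

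**5. Zero events.** The one-sided 95% upper bound for 0/n is 1 − 0.05^(1/n).

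- On the 62 per arm of 2.8: 4.7% for 0/62, against 9.2% for the 31 scanned.
- On the 31 per arm of 2.2: 9.2% for 0/31, against 17.1% for about 16 scanned (31 × 0.5 = 15.5).

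**6. Between arms.** With s = 0, the reported ratio is [(1 − d₁)p₁]/[(1 − d₀)p₀], where p is the risk in completers of each arm. If d and RR are the same in both arms, the bias factor cancels and the ratio is unbiased; an absolute difference shrinks by that factor. If d or RR differs between arms, the ratio is biased too.

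**The case against.** The strongest reply is that the article nowhere says that unscanned participants count as ARIA-free. It says only that "occurrences of ARIAs will be monitored", and the denominator for one scan-based item is a detail that a condensed article can leave to the analysis plan. This stands in part: the result is a consequence of stated rules, not a stated intention. But the two rules that produce it, ITT for safety and LOCF for missing data, are both fixed in the article without an exception. An analyst who follows them as written reaches this result.

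Several stronger readings are tempting and are not supported.

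- *That ARIA can be seen only at weeks 26 and 32.* Those are the scheduled scans. Clinically prompted scans are neither described nor excluded.
- *That incidence will be halved.* Halving needs every one of the 50% to leave before week 26, none to have a later scan, and equal risk in drop-outs and completers. The 50% is a planning figure without timing, and someone lost between weeks 26 and 32 still has a week 26 scan.
- *That the plan claims too much precision for ARIA.* It states none. The bounds above show what would follow if a bound were reported.
- *That the comparison favours one arm.* Nothing in the article points to different drop-out by arm.
- *That ITT is the wrong safety population.* It suits reported adverse events and should stay for them.

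It is also fair to object that a scanned-only denominator is no complete cure: it is unbiased only at equal risk, as step 4 shows. That stands, and it is why a sensitivity analysis belongs in the repair.

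**Conclusion.** The point holds as a conflict between stated rules. With MR scheduled only at weeks 0, 26 and 32, ITT for safety and an unrestricted LOCF rule, a participant who leaves before week 26 without a later scan is recorded as having no new ARIA. Absolute incidence is biased downward, and any upper bound on it is too favourable.

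At equal risk the size runs from 0.50 of the true value (all of the assumed 50% unscanned) through 0.75 (half of them scanned) or 0.80 (20% drop-out, all unscanned) to no bias if every drop-out has a post-baseline scan. If drop-outs carry more risk than completers, it can fall below 0.50. With half of participants unscanned and no events, the upper bound is about half of what the scanned data support, whether 2.2 or 2.8 gives the right sample size.

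This assumes that LOCF is applied to ARIA as 2.7 literally reads and that the full ITT count is the denominator. It is worth correcting before analysis. It does not affect the primary outcome or the count of adverse events.

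**What to change.** - **2.9:** report ARIA among participants with a baseline MR and at least one post-baseline MR, and give the number unscanned in each arm. Keep ITT for reported adverse events.
- **2.7:** exempt ARIA from LOCF.
- **2.9:** add a sensitivity analysis that assigns unscanned participants a range of ARIA risks relative to those scanned, allowed to differ by arm.
- **2.6:** describe the outcome as new ARIA seen on a post-baseline scan.
- **2.2 and 2.8:** reconcile 31 and 62 per arm, because the expected number unscanned depends on which applies.

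The cost is wording and one small additional analysis; the scan schedule does not change. The downside is a smaller denominator and a wider, less favourable interval, which reflects what was actually observed.
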